### Gait and Physical Activity Assessment Using Wearable Sensors

Monitoring using wearable inertial devices [SBG analyses that includes 3-axial accelerometers and gyroscopes (Physiolog5^®^, Gait Up, Switzerland)] will allow an objective quantification of motor activity in daily life, during the course of the study three times for 1 week during the daytime (before and after 3 weeks of training and after 3 months following the intervention; Figure 2). Synchronized inertial devices will be attached to both feet (two sensors fixed by a clip on the shoes or at the ankle with a tape) and at the lower back (one sensor fixed with a double-sided adhesive tape and secured with a band-aid at the area of the fourth and fifth lumbar vertebrae) to record accelerations and angular velocity of the respective body segments. The study nurse and an instruction sheet will explain the use of the sensors at home for the week before the first visit (V1). The sensors for the week after V2 and the week before V3 will either be sent and/or collected by regular mail or given and/or collected during the appointments. A protocol with four columns (FoG, sports and therapy, weather and activities, and particularity) will be given to the patient. Recorded data will be transferred *via* online sharing to the Laboratory of Movement Analysis and Measurement, École Polytechnique Fédérale de Lausanne (EPFL), Lausanne, Switzerland. It will be processed using validated state-of-the-art algorithms (37–41) to characterize the multiple dimensions of gait and physical activity. More specifically, the parameters extracted will be related to.

#### Ambulatory Activity and Walking Behavior

Step count [number per day], distribution of walking bout duration [seconds], the timing of walking activity over the course of the day [% of time spent walking in the morning vs. afternoon], and indicators of walking performance, expressed, for example, as the percentage of long walking bouts with fast and regular speed [%] (42).

#### Gait Pattern

Spatio-temporal gait parameters, such as speed [m/s], cadence [steps/min], stride length [m], swing/stance/double support phases [% of gait cycle duration], variability [unitless], and asymmetry [unitless].

#### Turning

Automatic detection of turning and estimation of gait parameters, step count, and movement smoothness during the turning period. Detailed characterization of turning is expected to provide further insights into postural instability and fall prediction, as it requires multi-limb coordination and continuous displacement of the body center of mass, and it is regularly performed during daily activities [it is estimated that up to 50% of strides taken during daily activities are turning strides (43)]. On top of being a significant motor parameter of gait performance, turning behavior is an important dopamine-mediated predictor of neuropsychiatric symptoms [e.g., (44, 45)]. Novel therapies focusing on turning can improve clinical outcomes in PD, such as the frequency of falls (46).

#### Freezing of Gait

Combined inertial data from feet and lower back sensors will be used to extract a set of features that will be used to identify FoG episodes using machine learning-based algorithms (47), previously developed and validated on similar datasets (48, 49).

All the analyses will be performed by processing the raw sensor data [i.e., acceleration [gravity units, g] and angular velocity (degrees/s)] using algorithms implemented in MATLAB (MathWorks Inc, Portola Valley, CA, USA).

### Gait Analyses of the C-Mill Data

Three minutes of walking with the comfortable velocity will be used for gait analyses at V1 and V2 (Figure 2) (at the same velocity as at V1). The following parameters will be determined: velocity [m/s], distance [m], steps [number], and step frequency [number/time unit]. Step length [m], stand time [min], and step width [m] will be calculated for both feet separately. In addition, the raw data will be processed by using MATLAB (MathWorks Inc, Portola Valley, CA, USA).

### Sample Size

According to previous studies, a reduction of 50% in the frequency of falls or near falls can be expected in the two experimental intervention groups vs. a reduction of 25% in the control group. Under the assumption of a difference of 1.5 falls between the respective group and placebo and an SD of 1.16, a sample size of 15 patients in each group is required (alpha = 0.025 two-tailed, power = 80%), i.e., 10% dropouts (G-power) (11).

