## Introduction

Falls occur with a high prevalence of about 60% in patients with Parkinson's disease (PD) with 40% having recurrent falls with an average of 20 falls per year (1). Stooped posture, increased sway, turning deficits, slowed integration of somatosensory information, reduced postural, and anticipatory adjustments are important factors contributing to reduced balance (2). Already in an early stage of PD, diminished gait speed, pain, history of falls or near falls, balance disturbances during dual-tasking (DT), retropulsion, freezing of gait (FoG), and the need for stabilization assistance are associated with falls (3). When controlled for age and sex, only fear of falling, history of near falls, and retropulsion predict prospective falls (3). In later stages, the akinetic-rigid motor type, motor fluctuations (off-phases and dyskinesia), high L-dopa dosage, FoG, and anxiety predict falls (4, 5). At these stages, falls are further predicted by impaired postural stability and by impaired cognitive function. In particular, attention, executive function, and specifically the capability of DT predict future falls (6, 7).

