## Materials and Methods

### Study Design

Patients with PD will be assigned randomly to one of three different training programs (AR-TT, or RNG- TT, or TT alone), which will be performed in a parallel-group design for 3 weeks of 30 min daily for 5 days a week in addition to the regular rehabilitation program (Figures 1, 2). Frequency of falls or near falls (within 3 months before V1) will be used (x > 1 or x = 1) for stratified randomization.

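### The Sample Size assumptions do not fit together: an SD of 1.16 is too small for the fall counts implied by the stated reductions, and with Poisson variation the power is about 36–46%, not 80%

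*Protocol article*

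**What the plan says.** The primary outcome (Study Design) is the frequency of falls or near-falls in the 3 months after training, set against the 3 months before inclusion. Each dual-task arm is compared with TT alone.

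The Sample Size section makes two kinds of assumption about this outcome:

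- Relative: "a reduction of 50% in the frequency of falls or near falls can be expected in the two experimental intervention groups"; for the comparator arm the assumed drop is half as large, 25%.
- Absolute: "Under the assumption of a difference of 1.5 falls between the respective group and placebo and an SD of 1.16".

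From the absolute pair it derives 15 patients per group at "alpha = 0.025 two-tailed, power = 80"%, with 10% dropout. It states no baseline mean and does not say which quantity the SD describes.

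Two other places bear on the size of the counts. The Introduction describes PD patients as having falls in about 60%, with "40% having recurrent falls with an average of 20 falls per year". The Study Design section says: "Frequency of falls or near falls (within 3 months before V1) will be used (x > 1 or x = 1) for stratified randomization". The Statistics section plans a mixed-effect ANOVA with baseline values as covariates and a log transformation of non-normal variables.

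**The concern.** The relative and absolute assumptions appear in one paragraph and concern the same outcome, so they should describe the same counts. Together they fix the baseline mean, and the baseline mean limits how small the SD of an event count can reasonably be. The stated SD looks far too small for that mean.

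What is at stake is how the primary result will be read. A reader who trusts 80% power will take a non-significant contrast as evidence that dual-task training adds nothing. If the true power for the planned effect is nearer 40%, a non-significant result is the more likely outcome even when that effect is real.

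**Working it through.** **Inputs.** From Sample Size: reductions of 50% and 25%, difference 1.5, SD 1.16, two-sided alpha 0.025, 10% dropout, 15 per arm. Assumed for the check: equal baseline means (the Results section expects a similar distribution of falls across arms), and percentages and difference that describe the same 3-month counts.

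**1. Reproduce the plan's figure.** Standardised difference d = 1.5/1.16 = 1.293. For a two-sample t test, the non-centrality is d/√(2/n) with 2n − 2 degrees of freedom. Power is 77.1% at n = 12 and 81.1% at n = 13. Then 13/0.9 = 14.4, rounded up to 15. The stated n reproduces.

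**2. Implied counts.** Baseline B satisfies (0.50 − 0.25) × B = 1.5, so B = 6 events per 3 months. Follow-up means are 0.75 × 6 = 4.5 (TT alone) and 0.50 × 6 = 3.0 (dual-task arm). The rate ratio is 0.50/0.75 = 0.67. As a check on scale, 20 falls per year in recurrent fallers is 20/4 = 5 per 3 months.

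**3. SD of such counts.** If events occur at random at a given rate, the variance equals the mean. The SDs are √4.5 = 2.12 and √3.0 = 1.73; the pooled value is √((4.5 + 3.0)/2) = √3.75 = 1.94. The plan's variance is 1.16² = 1.35, and 1.35/3.75 = 0.36. The baseline covariate can remove differences between patients in their underlying rates. It cannot remove the random variation in each patient's count around that rate, which is what the 3.75 represents.

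**4. Power for 3.0 vs 4.5 with Poisson variance, alpha 0.025 two-sided.**

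| Method | n = 13 | n = 15 |
|---|---|---|
| t test, SD 1.94 | 35.6% | 41.5% |
| Log rate ratio, SE = √((1/4.5 + 1/3.0)/n) | 39.0% | 44.6% |
| Simulation, t test | 35.4% | 41.6% |
| Simulation, t test on log(x + 1) | 33.4% | 39.2% |
| Simulation, Poisson likelihood-ratio test | 39.8% | 45.8% |
| Simulation, variance pooled over three arms | 39.8% | 45.9% |

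The range is about 36–46%, and slightly lower after a log(x + 1) transformation. For scale, 80% power by t test would need 33 completers per arm, or 33/0.9 = 36.7, rounded up to 37.

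**5. Overdispersion.** Suppose the residual variance is mean + k × mean², with k = 0.25 as an assumption. The average variance is ((4.5 + 5.06) + (3.0 + 2.25))/2 = 7.41, SD 2.72. Power is 18–21% by t test and 21–24% for the log rate ratio.

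**6. Giving up one of the stated figures instead.**

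- Keep SD 1.16 and the percentages. The average follow-up mean is 0.625 × B = 1.3456, so B = 2.15. The difference is 0.25 × 2.15 = 0.54, and power is 13–15%.
- Keep SD 1.16 and the 1.5 difference. The means become 1.35 ± 0.75, about 2.10 and 0.60. That is a 72% relative reduction, against the 33% that the stated percentages give.
- Keep only the percentages, with Poisson variance and a t test at n = 13 and n = 15:

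| Baseline | Difference | Power |
|---|---|---|
| 2 | 0.50 | 12–14% |
| 5 | 1.25 | 30–35% |
| 8 | 2.00 | 47–54% |
| 10 | 2.50 | 57–65% |

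**The case against.** The strongest reply is that nothing has been miscalculated. The n follows from the stated difference and SD, and the dispute is about whether one input is plausible. That stands: this is an inconsistency among assumptions, not an arithmetic error.

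The baseline of 6 is derived, not stated. It rests on equal baselines and on the percentages and the difference sharing one scale. That is the natural reading of the paragraph, but it is a condition. Because near-falls count as well, the true baseline could exceed 6, and power would then be higher, as the last table shows. Such a baseline gives up the 1.5-event difference.

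Poisson variance is a modelling assumption and not a mathematical lower bound. Counts more regular than random can have a smaller SD. The figures are therefore conditional, and calling 36–46% the most the design could deliver would go too far. The k used for overdispersion is likewise an assumption.

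A reader might infer several stronger points that the document does not support:

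- **That a true halving of falls would probably be missed.** The underpowered contrast is 50% vs 25% reduction, a rate ratio of 0.67. A true halving relative to TT alone (2.25 vs 4.5) has 76–83% power under the same Poisson assumption.
- **That the cited source (11) is the wrong one.** The article describes it elsewhere through its imaging results, but whether it also holds fall data cannot be checked here.
- **That the Poisson SD of an unadjusted change score (about 3.1) applies.** The planned model adjusts for baseline.
- **That the trial must be relabelled a pilot.** That is one option among several, and the inconsistency does not require it.

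**Conclusion.** The power statement is wrong as written. The four figures in the Sample Size section cannot all hold for a 3-month event count unless falls are far more regular than random, with about 0.36 times Poisson variance, and the article offers no basis for that.

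Conditional on a baseline of 6 events and Poisson variance, the planned contrast (rate ratio 0.67) has about 36–46% power with 13–15 per arm. Residual overdispersion lowers this, for example to 18–24% at an assumed k = 0.25. Keeping the SD and the percentages instead gives 13–15%. A higher baseline raises power, to 57–65% at 10 events, but no longer matches the stated difference. None of these alternatives supports 80% for the assumptions as printed.

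**What to change.** Restate the power in the Sample Size section without enrolling more patients:

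- State the assumed baseline mean and dispersion of the 3-month count.
- Express the effect as a rate ratio of 0.67 (0.50/0.75).
- Replace 80% with the power that 45 patients give under those assumptions, about 36–46% at baseline 6 with Poisson variance.
- Report the primary comparison with its effect estimate and confidence interval, so that a non-significant result is not read as absence of benefit.
- Name the comparator as TT alone where the section says placebo.

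This is a change of wording only. The downside is a less favourable stated power.

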**Figure 2 F2:**
[figure not shown]
Experimental protocol design. MMSE, Mini-Mental Status Examination; Mini-BEST, Mini-Balance Evaluation Systems Test; SBG, sensor-based gait analyses; FoG, freezing of gait; WOQ-9, Wearing-Off Questionnaire-9; PDQ8, QoL in PD questionnaire; HADS, Hospital Anxiety and Depression Questionnaire; MDS-UPDRS, MDS-sponsored revision of the Unified Parkinson's Disease Rating Scale; CGIC, Clinical Global Impression of Change; TAP, Test Battery of Attentional Performance.

Assessments will be performed by a blinded investigator before the beginning of the training (V1), after 3 weeks of training (V2), and 3 months after training (V3) during the on-phase. The primary outcome will be the frequency of falls or near-falls during 3 months following training compared to the frequency of falls or near-falls in the 3 months before inclusion (AR-TT vs. TT, and RNG-TT vs. TT). Both interventions will be compared in exploratory analyses (AR-TT and RNG-TT).

Secondary outcomes will be the clinical parameters Movement Disorder Society-sponsored revision of the Unified Parkinson's Disease Rating Scale (MDS-UPDRS III-IV) (25), Hospital Anxiety and Depression Questionnaire (HADS) (26), FoG Questionnaire (27), the Mini-Balance Evaluation Systems Test (Mini-BEST) (28), quality of life in PD questionnaire (PDQ-8) (29), Wearing-Off Questionnaire-9 (WOQ-9) (30), and executive function testing by using tests of the Test Battery of Attentional Performance (TAP) (31) assessed at V1, and compared to V2 and V3 (MDS-UPDRS III-IV, HADS, FoG Questionnaire, Mini-BEST only). Clinical Global Impression of Change (CGIC) will be assessed and V2 and V3 (32).

Sensor-based gait (SBG) assessment will be measured and compared before V1, after V2, and before V3 to have more detailed information on gait changes in the natural environment at home. Given the set of parameters described in Section “Gait and Physical Activity Assessment Using Wearable Sensors,” analyses will be conducted to evaluate the sensitivity to change related to a progression in daily-life motor performance following the rehabilitation program. In addition, gait analysis on behalf of the C-Mill data will be collected before and after the intervention during 3 min of comfortable walking (V1 and V2).

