### Patients

In total, 45 PD patients (age 40 or older) with Hoehn and Yahr stages II-IV (only mobile patients with advanced PD), with at least one fall or near-fall within the 3 months before baseline assessment, will be asked for participation when appointed to in-ward neurorehabilitation at the Center for Neurorehabilitation in Valens, Switzerland (Figure 1). Patients shall be able to participate in the treadmill training at high intensity for 3 weeks. Patients with dementia, defined by a Mini-Mental Status Examination (MMSE) test result of <24, will be excluded from participation. The protocol was approved by Ethikkommission Ostschweiz (BASEC ID 2019-01894) and registered at ClinicalTrials.gov (Identifier: NCT04108741).

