### Statistics

Numerical variables will be described with means and SDs, and categorical variables by percentages. The numerical outcomes in this study will be analyzed by a mixed-effect ANOVA model, using treatment and visit as fixed factors, subject as a random factor, and baseline values as covariates. A planned contrast will be used to compare data at month 3 between the groups. Non-normally distributed variables will be log-transformed. Imbalances in the characteristics of the groups at baseline will be included in the ANOVA model as part of a sensitivity analysis. The statistical analysis will be conducted in R 4.1.1 (The R Foundation, Vienna, Austria).

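### Testing the two primary comparisons by Holm at a family-wise 0.05, instead of at a fixed 0.025 each, would add power with the same 45 patients (optional gain, not an error in the plan)

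*Protocol article*

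**What the plan says.** In Study Design (the text after Figure 2) the Protocol article defines the primary outcome, falls or near-falls over the three months after training relative to the three months before inclusion. It names two comparisons for it: "AR-TT vs. TT, and RNG-TT vs. TT". The contrast between the two dual-task arms is set apart: "Both interventions will be compared in exploratory analyses (AR-TT and RNG-TT").

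Sample Size gives one significance level, the only one in the document. "Under the assumption of a difference of 1.5 falls between the respective group and placebo and an SD of 1.16", the article states that "a sample size of 15 patients in each group is required (alpha = 0.025 two-tailed, power = 80"%), and dropout is mentioned directly after: "i.e., 10% dropouts (G-power"). The same section expects a 50% reduction in both experimental arms against 25% in the control arm. Results repeats the expectation that both dual-task programmes will do better than TT alone.

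Statistics describes a mixed-effect ANOVA and then says: "A planned contrast will be used to compare data at month 3 between the groups". It gives no level and no multiplicity rule of its own.

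**The concern.** Two primary comparisons and a level of 0.025 for each add up to 0.05, so the natural reading is an equal Bonferroni split, although the article does not use that name. The split protects the family-wise error, but it holds the second comparison to 0.025 even after the first has been declared significant. That is stricter than a 5% family-wise error requires.

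Holm's procedure uses the same 0.025 for the smaller p-value and, only if that rejects, 0.05 for the larger. It rejects everything the equal split rejects and sometimes one comparison more. In a trial with 13 to 15 evaluable patients per arm, whose stated hypothesis is that both programmes beat TT, the stake is the chance of demonstrating the second effect.

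**Working it through.** **Inputs.** From Sample Size: difference 1.5 falls, SD 1.16, two-sided 0.025 per comparison, power 80%, dropout 10%, 15 per group. From Study Design: two comparisons with a shared TT arm. From Patients: 45 in total, which is 3 × 15.

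**Reproducing the plan's figure.**
- Standardised difference: d = 1.5 / 1.16 = 1.293.
- Normal approximation: n = 2 (z₀.₉₈₇₅ + z₀.₈₀)² / d² = 2 (2.241 + 0.842)² / 1.672 = 11.4, so 12 per arm, and 12 / 0.90 = 13.3, so 14 with dropout.
- Noncentral t, with df = 2n − 2 and noncentrality d√(n/2): n = 12 gives power 77.1%; n = 13 gives noncentrality 3.297, critical value 2.391 and power 81.1%. So 13 per arm are needed, and 13 / 0.90 = 14.4, so 15.

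The stated 15 per group is reproduced by the t-based calculation at 0.025. The split level therefore drives the design.

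**Comparing the two rules.** Three arms of 13, normal outcomes, shared control, variance pooled over three arms (36 df), two-sided tests, 1,000,000 simulated trials per scenario:

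| Scenario | Quantity | Fixed 0.025 each | Holm at 0.05 |
|---|---|---|---|
| Both arms work (1.5 each) | Power per comparison | 82.6% | 87.1% |
| | Power to win both | 72.7% | 81.7% |
| | Power for at least one | 92.5% | 92.5% |
| Only one arm works | Power for that arm | 82.6% | 82.8% |
| | False positive in the other arm | 2.5% | 4.3% |
| Neither works | Family-wise error | 4.6% | 4.6% |

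The noncentral t with 36 df gives 82.6% for the fixed rule directly, which agrees with the simulation.

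**Where the gain comes from.** Holm adds a rejection only when one p-value is below 0.025 and the other lies between 0.025 and 0.05. The gain in winning both is therefore the sum of the two per-comparison gains: about 4.5 + 4.5 = 9 points, as the table shows (81.7 − 72.7 = 9.0). For the same reason the chance of at least one success cannot change, because the first step is identical under both rules.

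**Sensitivity.**
- With ordinary two-sample t-tests, each using its own two arms, the per-comparison figures at 13 per arm are 81.1% and 86.0%; for both comparisons they are 70.2% and 80.1%.
- With all 15 per arm evaluable and pooled variance, they are 88.4% and 91.9%; for both, 81.0% and 88.0%.

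The gain is of similar size each time.

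**The case against.** The strongest reply is that nothing here is wrong. An equal split is standard, controls the error rate and agrees with the sample size. That stands, so this is an efficiency suggestion and not a defect.

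A second reply is that the benefit depends on the scenario. That also stands. If only one programme works, Holm moves its power by 0.1 to 0.2 points, and the chance of at least one success does not move at all. The larger gains need both arms to be effective at about the assumed size. Sample Size and Results do assume this, but it is an assumption.

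A third reply is that Holm has a price in reporting. Under the equal split, 97.5% intervals match the tests exactly. Under Holm they do not: a comparison rejected at the second step can have a 97.5% interval that includes zero. This stands as a minor cost.

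A reader might go further and infer that, because Statistics repeats no level, the two contrasts could each be tested at 0.05, with a family-wise error of about 9%. The document does not support that. The only level it states is 0.025, nothing in it points to 0.05 per contrast, and a condensed article may leave the exact test rule to a fuller document. Nor does the singular wording about a planned contrast show that only one contrast is intended, since Study Design already names both and makes the third comparison exploratory.

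**Conclusion.** The fixed 0.025 per comparison is valid but gives away some power. Under the plan's own inputs, and if both arms work as assumed, Holm at a family-wise two-sided 0.05 adds about 4.5 points per comparison and about 9 points for winning both, with the same patients and the family-wise error still at or below 5%. If only one arm works, there is almost no gain.

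The power figures rest on normal outcomes with a common SD of 1.16 and simple comparisons of means. Fall counts may be skewed, and the planned mixed model with a baseline covariate will not match these figures exactly. Holm's error control and its advantage over the equal split need only valid p-values, so the direction does not depend on those assumptions. This is a cheap, optional improvement; the sample size and the error control of the plan are not in question.

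**What to change.** Add one sentence to Statistics before any unblinded look at the outcome: the two month-3 contrasts, AR-TT against TT and RNG-TT against TT, are tested by the Holm procedure at family-wise two-sided 0.05, the smaller p-value against 0.025 and, if that rejects, the other against 0.05. AR-TT against RNG-TT stays exploratory, as Study Design already states.

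Keep 15 per group, because Holm's first step still uses 0.025 and the existing calculation remains the right one for it. Report 97.5% confidence intervals for both contrasts alongside the Holm decisions, and note that an interval can include zero when a contrast is rejected at the second step. The change needs no extra patients and no extra data.
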